## Abstract

**Background:**

In Belgium, the construction of the national electronic point-of-care information service, EBMPracticeNet, was initiated in 2011 to optimize quality of care by promoting evidence-based decision-making. The collaboration of the government, healthcare providers, Evidence-Based Medicine (EBM) partners, and vendors of Electronic Health Records (EHR) is unique to this project. All Belgian healthcare professionals get free access to an up-to-date database of validated Belgian and nearly 1,000 international guidelines, incorporated in a portal that also provides EBM information from sources other than guidelines, including computerized clinical decision support that is integrated in the EHRs.

The EBMeDS system is the electronic evidence-based decision support system of EBMPracticeNet. The EBMeDS system covers all clinical areas of diseases and could play a crucial role in response to the emerging challenge posed by chronic conditions. Diabetes was chosen as the analysis topic of interest. The objective of this study is to assess the effectiveness of EBMeDS use in improving diabetes care. This objective will be enhanced by a formal process evaluation to provide crucial information on the feasibility of using the system in daily Belgian family medicine.

**Methods:**

The study is a cluster-randomized trial with before/after measurements conducted in Belgian family medicine. Physicians’ practices will be randomly assigned to the intervention or control group in a 1:1 ratio, to receive either the EBMeDS reminders or to follow the usual care process. Randomization will be performed by a statistical consultant with an electronic random list generator, anonymously for the researchers. The follow-up period of the study will be 12 months with interim analysis points at 3, 6 and 9 months. Primary outcome is the one-year pre- to post-implementation change in HbA1c. Patients will not be informed about the intervention. Data analysts will be kept blinded to the allocation.

**Discussion:**

The knowledge obtained in this study will be useful for further integration in other Belgian software packages. Users’ perceptions and process evaluation will provide information for improving the feasibility of the system.

**Trial registration:**

The trial is registered with the ClinicalTrials.gov registry: NCT01830569.

## Background and rationale

Evidence is of no use if it remains buried in the literature and is not implemented in practice. A first step is the conversion of evidence from studies into clinical practice guidelines. Point-of-care decision support systems based on electronic guidelines have been suggested to successfully deliver the knowledge embedded in Evidence-Based (E-B) guidelines [1,2]. A number of studies have already shown positive findings for some types of decision support systems such as drug-dosing systems and computer-based reminder systems for preventive care services [3,4]. The evidence is less clear for more complex electronic guideline implementation systems [5-9].

In Belgium, the construction of the national electronic point-of-care information service EBMPracticeNet was initiated in 2011 to optimize quality of care by promoting evidence-based decision-making. The National Institute for Health and Disability Insurance (INAMI-RIZIV) provides funding for this organization. The collaboration of the government, healthcare providers, Evidence-Based Medicine (EBM) partners, and vendors of Electronic Health Records (EHR) is unique to this project. All Belgian healthcare professionals get free access to an up-to-date database of validated Belgian and nearly 1,000 international guidelines, incorporated in a portal that also provides EBM information from sources other than guidelines, including computerized clinical decision support that is integrated in the EHRs. The link between all the EHRs from different vendors and a national database held on a single platform and controlled by all EBM organizations in Belgium is the strength of EBMPracticeNet [10].

The EBMeDS system is the electronic evidence-based decision support system of EBMPracticeNet. The EBMeDS system was developed by Duodecim [11] and will gradually be integrated in the different Belgian software packages. EBMeDS is currently being integrated in the software of HealthOne, one of the Belgian electronic medical record systems (EMR).

The main distinguishing feature of the EBMeDS system is its intuitive approach and its platform-independent, service-oriented architecture, with strong central management. This has been recognized as being critically important for keeping the evidence up-to-date and for integrating the system in the different software packages used by all physicians involved in the care processes. In addition, the involvement of end-users during the implementation process is a critical feature of its success [12,13].

The EBMeDS system covers all clinical areas of diseases and could play a crucial role in response to the emerging challenge posed by chronic conditions such as hypertension, diabetes, and heart failure, etc. Chronic conditions increasingly affect the population and could lead to serious complications and disability in the long term if not managed appropriately in a proactive healthcare system. Chronic conditions require collaboration between different healthcare workers, recurrent visits, adherence to (sometimes overlapping or diverging) care plans and long-term disease and treatment monitoring [5]. Theoretically, the EBMeDS system has the potential to deal with these multifactorial dimensions of chronic diseases in ambulatory settings.

As with any health intervention, rigorous testing is warranted to determine whether the EBMeDS system could realize improvements in chronic care processes and, more especially, patient outcomes. Based on the results of a previous qualitative study in a pilot setting, we adapted the mode of evidence delivery and the quantity of reminders of a previous version of the system to prevent reminder fatigue [14].

Diabetes was chosen as the analysis topic of interest. Type II diabetes mellitus is a highly prevalent disease and at the moment the leading cause of blindness, renal dysfunction, non-traumatic limb amputation, and decreased life expectancy [15]. Optimal care of diabetes patients has been difficult to achieve because of the difficulties in sustaining regular monitoring and attention to many risk factors over many years [16]. Clear recommendations on the basis of high levels of evidence exist to prevent these complications, but there is still a large gap between recommended care and the care that patients actually receive [17,18].

The objective of this study is to assess the effectiveness of EBMeDS use in improving diabetes care as a case study. This objective will be enhanced by a formal process evaluation to provide crucial information on the feasibility of using the system in daily Belgian family medicine.

## Methods

The study is a cluster-randomized trial with before/after measurements conducted in Belgian family medicine. A cluster design is necessary to minimize contamination that might occur if individual patients were randomized. Randomization will be performed at practice level; the intervention will happen at physician level; and data will be analyzed at patient level, in a multilevel analytical approach. The follow-up period of the study will be 12 months.

Physicians’ practices will be randomly assigned to the intervention or control group in a 1:1 ratio, to receive either the EBMeDS reminders or to follow the usual care process.

### Participants and setting

Physicians eligible to participate in the study are all family physicians (739 Dutch-speaking and 891 French-speaking) using HealthOne (1,630 family physicians). Physicians will be included if the following criteria are met:

1. The physician has integrated HealthOne in his consultations;

2. The physician uses the functionality of e-prescribing within HealthOne so that prescribed medication can be identified from the electronic medical records; and

3. The physician agrees to be involved in the study.

Patients are included if:

1. They are 18 years or older.

2. They have their electronic medical records registered with one of the participating family physicians. Medical records are not centralized in Belgium. Patients are free to choose any physician, and can even see several physicians at the same time. To encourage a patient to have their medical records held by a single physician, a voluntary enlisting program was introduced (Global Medical File) a decade ago. For every enlisted patient, the general practitioner who keeps their central medical records receives a registration fee. Enlisted patients are reimbursed to a larger extent by the health insurance fund.

3. They are enlisted and have an established diagnosis of diabetes at the baseline time point of the study (identified as having: an ICPC code of diabetes; or a prescription for a diabetes-specific drug; or the necessary laboratory results to confirm diabetes).

Exclusion criteria are pregnancy and cognitive impairment.

### Interventions

#### Trial preparation

To ensure that the point-of-care information provided through the EBMeDS system is context-sensitive, EBMPracticeNet had the responsibility to tailor the diabetes reminders and suggestions. Diabetes reminders were adapted to the Belgian context in collaboration with Domus Medica, a Belgian organization delivering evidence-based information for primary care. This adaptation process also included careful selection of the most relevant messages for the Belgian family physician, taking into account the risk of alert fatigue.

### The EBMeDS system in the intervention groups

The EBMeDS system receives structured patient data from the electronic medical records in HealthOne and returns reminders, therapeutic suggestions, and diagnosis-specific links to guidelines. Electronic forms and calculators (*e*.*g*., a calculator for glomerular filtration) are integrated in the system.

The original EBMeDS system covers a full spectrum of all clinical areas. Relevant reminders in all clinical areas are shown to the physicians in the intervention group, but analysis is limited to the treatment and follow-up of diabetes patients.

HealthOne is one of the electronic medical record systems in Belgium. The software enables physicians to record patient histories and contacts, to display test results, to access generated notes and reports, and to support physicians in decision-making for patient care.

### The evidence Linker in the control and intervention groups

The Evidence Linker has been integrated in Belgian routine practice since 2012 and could be considered part of the usual care process. When entering a diagnosis coded in ICPC, relevant clinical practice guidelines are retrieved by the Evidence Linker and can by consulted on the initiative of the family physician.

The Evidence Linker service is offered by the Belgian Centre for Evidence-Based Medicine (CEBAM) and is available to all physicians in the control group as well as in the intervention group during study follow-up.

The content and recommendations of the diabetes guidelines presented in the Evidence Linker are similar to the content of the EBMeDS diabetes reminders. Differences between the intervention and control groups are the method of evidence delivery (‘push’ versus ‘pull’) and the format of the recommendations (‘guideline format, long’ versus ‘reminder format, short’).

### Objectives

The objective of this study is to assess the feasibility of the use of the EBMeDS system in daily Belgian family medicine and to study the effectiveness of EBMeDS use in improving diabetes care according to current evidence-based guidelines. Specific research questions are:

1. Do family physicians use the EBMeDS system in daily practice?

2. Does the use of the EBMeDS system by family physicians lead to an improvement in diabetes control compared to the control group?

3. How do family physicians perceive the reminders included in the EBMeDS system?

### Outcomes

#### Baseline measurements

Baseline demographic data on patient age, gender, years since the diagnosis of diabetes, nursing home residence (yes/no), HbA1c, cholesterol levels, and blood pressure will be collected. Data on physician age, gender, years of experience, and native language will be requested as well.

### Primary and secondary outcomes

Primary outcome is the one-year pre- to post-implementation change in HbA1c.

Secondary outcomes are the one-year differences in cholesterol levels and systolic and diastolic blood pressure. A composite patient score and a composite process score are calculated representing the change in diabetes (process) control and associated cardiovascular risk [19]. The composite patient score consists of reaching the evidence-based targets for glycated hemoglobin, blood pressure (systolic and diastolic), and cholesterol. The process composite score consists of meeting the evidence-based targets of the number of blood pressure measurements, the number of laboratory results of HbA1c, cholesterol and micro-albuminuria, a prescription of statin (yes/no), if high cardiovascular risk a prescription of aspirin/clopidogrel (yes/no), if hypertension or nephropathy ACE inhibition/sartan (yes/no).

Outcomes that cannot be reliably detected from the electronic medical records such as smoking status, and feet and eye examinations are excluded from the composite scores, as well as outcomes in which family physicians’ influences are minimal (*e*.*g*., BMI, physical activity, etc.).

Outcomes of the composite scores with their respective targets are shown in Table 1. Recommendations and targets are based on the diabetes guidelines of Domus Medica [20] and the Belgian ‘Zorgtraject diabetes’ [21].

**Table 1 T1:** Variables included in the composite scores

***Variable***	***Process target***	***Maximum score per period****	***Clinical target***	***Maximum score per period***^**†**^
HbA1c	Quarterly	2	< 7%	1
Blood pressure	Quarterly	2	< 130/80 mm Hg	1
Cholesterol (LDL, HDL, Total)	Annual	1	LDL < 100 mg/dL	1
Microalbuminuria check	Annual	1		
A prescription of statin	Yes/no	1		
If high cardiovascular risk, a prescription of aspirin/clopidogrel	Yes/no	1		
If hypertension or nephropathy, ACE inhibition/sartan	Yes/no	1		
Total		9		3

*Maximum score for process composite per period = 9 (7 variables).

^†^ Maximum score for patient composite per period = 3 (3 variables).

Each of the parameters in the composite scores is compared with their respective target. Each outcome that meets the target will be assigned one point. If all outcomes meet the targets, a maximum score of 3 points will be assigned to the patient composite score and a maximum score of 9 points will be assigned to the process composite score. If we cannot find any data about the process variable, we will assume that it did not happen. A variable that improves during the intervention period will be scored as +1; each variable that worsens will be scored as −1; and each variable that does not change will be scored as 0. As such, composite scores can be grouped into three categories: worsened, unchanged or improved.

The follow-up period will be 12 months. Outcomes will be collected at five points: before the start of the study, at 3 months, at 6 months, at 9 months and at 12 months, with the differences between pre- and post-implementation forming the outcome scores. A mean will be calculated for the intervention and control groups. The trial will be terminated at one of the interim analysis points when a mean difference of 0.3% might be reached for the primary outcome of HbA1c change.

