### Process evaluation

In the process evaluation, actual use of the system as well as users’ perceptions about the feasibility of the electronic decision support will be measured. These aspects are two necessary components of a process evaluation [22].

Scripts are automatically triggered, and users can see that a script is available from their main screen but have to click to view the script content. As such, click events can give us an indication of physicians’ interest in using the system. A new record is inserted in the log file for each script that is triggered. The following data of actual use are collected in a log file at the physician level: identification code of the script; type of script that is triggered and opened (Reminder, Interaction, Contra-indication, Drugs to avoid, Indication, GuideLine Link); script node expanded (yes/no): *e*.*g*., a long reminder displays when a short reminder is clicked; request for the script information (yes/no).

As such, the percentage and the type of scripts that were opened will be calculated, as well as the percentage of scripts that were expanded and the percentage of scripts for which the script information was requested.

Process information regarding actual use of the Evidence Linker will be logged in a similar way.

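### The process composite scores any withdrawal of a statin, aspirin/clopidogrel or ACE inhibitor/sartan as worsened care, while only the EBMeDS arm is pushed contra-indication and drugs-to-avoid scripts

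*Protocol article*

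**What the plan says.** The section on primary and secondary outcomes defines the process composite, and Table 1 gives its points: "Maximum score for process composite per period = 9 (7 variables". One point each goes to a statin prescription, with no condition attached, and to two conditional items: "if high cardiovascular risk a prescription of aspirin/clopidogrel (yes/no" and "if hypertension or nephropathy ACE inhibition/sartan (yes/no". Both conditions concern who has an indication. Neither concerns who has a reason not to receive the drug.

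The same section then fixes how change is scored. An item that improves earns +1, "each variable that worsens will be scored as −1", and no change earns 0. The result is grouped as worsened, unchanged or improved. A process item with no data is taken as not done.

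On the intervention, the section on the EBMeDS system states: "Relevant reminders in all clinical areas are shown to the physicians in the intervention group". The process evaluation section lists what is logged: "type of script that is triggered and opened (Reminder, Interaction, Contra-indication, Drugs to avoid, Indication, GuideLine Link". The section on the Evidence Linker describes the control arm as guidelines that the physician looks up, a pull as opposed to a push.

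The data analysis section compares the three-level scores between arms with random-effects proportional odds models. Baseline-category logit models are the fallback if proportionality fails. Similar models, restricted to the intervention arm, relate actual EBMeDS use to the outcomes.

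**The concern.** A yes/no prescription item has only one way to worsen, which is from yes to no. The rule does not ask why the drug was stopped. Consider a patient on one of these drugs at baseline whose physician opens a warning script and withdraws the drug. The item scores −1, and if nothing else changes the patient is classed as worsened. The same patient in a control practice, with no pushed warning and the drug continued, scores 0 and is classed as unchanged.

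The prompt for this kind of withdrawal exists in one arm only, so randomisation does not balance it. Where it occurs, the safety content of the intervention is counted as poorer diabetes care. The use-outcome analysis is exposed in the same way: physicians who open and act on safety scripts would contribute lower process scores, which pulls the association between use and outcome downwards.

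**Working it through.** **Table 1 total.** The item maxima sum to 2 + 2 + 1 + 1 + 1 + 1 + 1 = 9 over 7 variables, as stated. The drug items supply 3 of the 9 points and 3 of the 7 variables.

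**Item scoring.** With 1 for a prescription and 0 for none, the change score is the sign of follow-up minus baseline: 0→0 gives 0, 0→1 gives +1, 1→1 gives 0, 1→0 gives −1. A withdrawal always scores −1. Taking the composite change as the sum of the item changes, one withdrawal with all else unchanged gives −1, which is worsened. If the item were not applicable in both periods, the sum would be 0, which is unchanged.

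**Illustration of size.** The documents give no rate of script-driven withdrawal and no expected category split, so the following inputs are assumptions.

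- Control arm: 25% worsened, 45% unchanged, 30% improved.
- True common odds ratio in favour of EBMeDS: 1.30.

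Intervention arm before any script-driven withdrawal:

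- Odds of not worsened: (0.75/0.25) × 1.30 = 3.90, so worsened = 1/4.90 = 0.2041.
- Odds of improved: (0.30/0.70) × 1.30 = 0.5571, so improved = 0.5571/1.5571 = 0.3578.
- Unchanged: 1 − 0.2041 − 0.3578 = 0.4381.

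Now move a share w of intervention patients from unchanged to worsened. The odds ratio at the worsened cut is [(1 − p)/p]/3, with p = 0.2041 + w. The odds ratio at the improved cut does not move. The common odds ratio comes from a maximum-likelihood proportional odds fit to the two distributions, with equal arms and no random effects.

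| w | p (worsened) | OR, worsened cut | OR, improved cut | Common OR |
|---|---|---|---|---|
| 0% | 0.2041 | 1.30 | 1.30 | 1.30 |
| 1% | 0.2141 | (0.7859/0.2141)/3 = 1.22 | 1.30 | 1.27 |
| 2% | 0.2241 | (0.7759/0.2241)/3 = 1.15 | 1.30 | 1.24 |
| 4% | 0.2441 | (0.7559/0.2441)/3 = 1.03 | 1.30 | 1.18 |

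If the 4% is split, with half moving from unchanged to worsened and half from improved to unchanged, then worsened is 0.2241 and improved is 0.3378. The odds ratios at the two cuts are 1.15 and (0.3378/0.6622)/(0.30/0.70) = 1.19, and the common odds ratio is 1.17.

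**The case against.** The strongest reply is that the causal link is possible but not documented. The list of script types describes a log file. No section says that a warning script exists for a statin, aspirin/clopidogrel or an ACE inhibitor/sartan, how often one fires, or that it advises stopping. A script must also be clicked before its content is seen. This stands, and it is why the size cannot be fixed from the documents.

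Several paths also weaken the effect. A switch from aspirin to clopidogrel, or from ACE inhibitor to sartan, keeps the item at yes. A drug prescribed earlier in a scoring period may still count as yes. A gain on another item can offset the −1. These points stand too, and they limit the share of patients whose category changes.

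A reader might infer that the scoring contradicts the intervention, or that the composite as a whole must come out against EBMeDS. The documents do not support either. The rule is the same in both arms, and the Reminder and Indication scripts may raise prescribing and earn +1. Only the contribution of warning-driven withdrawals has a known direction.

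A reader might also take the odds ratio of 1.03 at 4% as a sign that the effect is nearly erased. That figure belongs to the worsened cut alone. The planned model reports one common odds ratio, about 1.18 in the same scenario.

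Finally, the full protocol or analysis plan might contain an exemption. That cannot be excluded. However, the article sets out the items, the points, the rule for absent data and the change rule, and it attaches applicability conditions to two of the three drug items. As written, it fixes a rule without the exemption.

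**Conclusion.** The point holds in limited form. Under the stated rules every withdrawal of these drugs scores −1, and pushed safety scripts reach one arm only, so a withdrawal that follows such a script counts against EBMeDS. The bias is conservative: this mechanism cannot produce a false claim of benefit.

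It is confined to the process composite and the use-outcome analysis of that composite. A reader might extend it to the trial's main conclusion, but HbA1c, cholesterol, blood pressure and the patient composite contain no prescription item.

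The common odds ratios of about 1.27, 1.24 and 1.18 at 1%, 2% and 4% show sensitivity only. They rest on an assumed control split, an assumed true odds ratio of 1.30, assumed shares of affected patients who each move from unchanged to worsened, and a marginal fit without the planned random intercepts.

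**What to change.** In Table 1 and the scoring rule, mark a drug item as not applicable in both periods when a contra-indication, interaction or intolerance to that drug is already coded in the EMR at baseline. Use one code list, fixed in advance and applied identically to both arms.

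As a sensitivity analysis, report the process composite without the three drug items, which leaves 4 variables and 9 − 3 = 6 points, and report the drug items separately. The reduced composite is free of the mechanism altogether.

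Do not let the main score depend on contra-indications coded after randomisation. EBMeDS may itself prompt such coding, and the exemption would then differ by arm.

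The cost is a revised table and rule, a code list, and a few more coded fields in the automatic extraction. Two weaknesses remain. EMR coding is incomplete, and the discussion section says the records were deliberately not reorganised. Contra-indications that arise during follow-up are also not exempted in the main score, which is why the sensitivity analysis is needed. The change concerns outcome scoring only and implies no prescribing rule.

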### Sample size

Based on the data in the literature, a mean difference of 0.3% in HbA1c change could be considered clinically significant (SD of HbA1c change 1.3%) [23-25]. To detect a mean difference of 0.3% in HbA1c change at four post-treatment occasions, with a two-sided unpaired *t*-test, a 5% family-wise significance level and Bonferroni correction for multiple testing, 1:1 allocation and a power of 80%, a sample size of 463 patients in each group will be necessary, assuming a withdrawal rate of 10%. Additional adjustment for clustering of patients within physician practices by the design effect [26], assuming 10 patients per cluster and an intra-class correlation coefficient of 0.047 based on data in the literature [27], leads to a sample size of 659 patients in each arm. Sample size calculations were based on historical data. They can be adjusted after baseline registrations if correct standard deviations and intra-cluster correlation coefficients are known. Sample size calculation was performed using SAS software.

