### Data analysis

Descriptive statistics will be provided regarding baseline variables of the patients and the family physicians. Intervention and control groups will be compared regarding baseline variables to evaluate the randomization. Linear mixed models will be used for continuous patient-level variables, with a random intercept to account for clustering of patients within physician practices. Logistic regression models based on generalized estimating equations (GEE) to account for clustering will be used for binary patient-level variables.

Differences between intervention and control groups regarding continuous outcome measures (change versus baseline in HbA1c, cholesterol levels, and blood pressure) will be assessed using linear mixed models (multilevel regression models) with random intercepts for physician practices and random intercepts for patients to account for repeated measurements over time. The primary fixed effect of interest will be the difference between intervention and control group, which will be tested at each time point (3 m, 6 m, 9 m and 12 m). If important differences in baseline characteristics are demonstrated between both groups, we will account for that by including the relevant variables in the model.

Differences between intervention and control groups regarding three-level composite scores (worsening, unchanged, improvement) will be assessed using random-effects proportional odds models, or, in case the proportional odds assumptions do not hold, baseline-category logits models, with random intercepts for physician practices and random intercepts for patients to account for repeated measurements over time. As with the analysis of continuous outcomes, differences between intervention and control groups will be tested at all time-points, and correction for imbalance in baseline characteristics will be applied if indicated.

To study the effect of the actual use of the EBMeDS system on the outcome measures, models similar to those described above will be used for analyzing the effect of intervention. However, they will now include a measure for the use of EBMeDS as the main explanatory variable, and will restrict analysis to the data obtained in the intervention group.

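### Both composite outcomes are tested only as worsened, unchanged or improved, without the baseline score as a planned covariate: valid, but inefficient

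*Protocol article*

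**What the plan says.** In the protocol article, Primary and secondary outcomes defines two secondary composites: "a maximum score of 3 points will be assigned to the patient composite score and a maximum score of 9 points" for the process composite. Each variable is also scored for change: plus one if it improves, minus one if it worsens, zero otherwise. The section then says that "composite scores can be grouped into three categories: worsened, unchanged or improved". No rule is given for combining the item scores into a category.

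The word "can" might leave the grouping optional, but Data analysis does not. There, "three-level composite scores (worsening, unchanged, improvement) will be assessed using random-effects proportional odds models", with baseline-category logits as fallback, random intercepts for practice and patient, and a test at 3, 6, 9 and 12 months. No test of the 0-3 or 0-9 score is described.

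Baseline adjustment is conditional on imbalance between the arms. The composite's own baseline value is not named as a covariate, nor is it listed under Baseline measurements. The Sample size section concerns HbA1c only.

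**The concern.** The full scores already exist, and the plan reduces them before testing:

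- A gain of one item and a gain of several are the same result. In Table 1, HbA1c and blood pressure monitoring carry up to two process points each, so a rise from 0 to 2 counts the same as a rise from 0 to 1.
- A patient with full control throughout and a patient with none throughout are both unchanged, although these are opposite states of diabetes control.
- If item changes are summed, which the text does not say, one gain and one loss also count as unchanged.
- A patient at the maximum cannot improve and a patient at zero cannot worsen, so the baseline score strongly predicts the category.

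The last point matters here because the Ethics section says that reminders appear when a patient's data depart from target. The intervention therefore acts where there is room to improve. At stake is power on both composite outcomes.

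**Working it through.** **1. The plan's own figure.** Inputs from Sample size: difference 0.3, SD 1.3, testing "at four post-treatment occasions, with a two-sided unpaired" t-test, 5% family-wise level with Bonferroni correction, 80% power, 10% withdrawal, and "assuming 10 patients per cluster and an intra-class correlation coefficient of 0.047".

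- Level per test: 0.05/4 = 0.0125.
- Normal approximation: n = 2 × (1.3/0.3)² × (2.498 + 0.842)² = 419 per arm. The t-test version gives 420.3.
- Withdrawal: 420.35 × 1.1 = 462.4, so 463. Dividing by 0.9 instead gives 467.1.
- Design effect: 1 + 9 × 0.047 = 1.423, and 463 × 1.423 = 658.8, so 659.

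The plan's 463 and 659 are reproduced. Both are for HbA1c. To gauge the composites I borrow the effective number analysed: 659 × 0.9 / 1.423 = 417 per arm.

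**2. Values lost.** Change in the patient score runs from -3 to +3 (7 values) and in the process score from -9 to +9 (19 values). If plus or minus one per variable is summed over the seven process variables, it runs from -7 to +7 (15 values). In each case three values remain.

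**3. Power.** Simulation with 417 independent patients per arm, items as dichotomised latent normals, the same latent shift on every item, and a two-sided 5% level. The effect was set so that the three-level test has about 73-82% power. A is the sign of the summed change (rank test, in effect the proportional-odds score test). B is the full change score. C is the follow-up score adjusted for the baseline score. RE is relative efficiency, and r is the assumed latent correlation between baseline and follow-up.

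| Composite | r | A | B | C | B-A | C-A | RE A/B | RE A/C |
|---|---|---|---|---|---|---|---|---|
| Patient | 0.30 | 79.8 | 84.5 | 96.5 | 4.7 | 16.7 | 0.863 | 0.540 |
| Patient | 0.50 | 78.9 | 83.1 | 93.7 | 4.2 | 14.8 | 0.884 | 0.620 |
| Patient | 0.70 | 80.0 | 83.6 | 91.3 | 3.6 | 11.3 | 0.903 | 0.710 |
| Patient | 0.85 | 77.2 | 81.1 | 86.4 | 3.9 | 9.2 | 0.929 | 0.797 |
| Process | 0.30 | 81.5 | 89.7 | 97.5 | 8.2 | 16.0 | 0.786 | 0.522 |
| Process | 0.50 | 80.0 | 89.4 | 95.4 | 9.4 | 15.4 | 0.786 | 0.589 |
| Process | 0.70 | 78.0 | 86.5 | 92.0 | 8.5 | 14.0 | 0.812 | 0.678 |
| Process | 0.85 | 73.2 | 80.5 | 84.8 | 7.3 | 11.6 | 0.827 | 0.743 |

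The three-level test needs 1/0.797 = 1.25 to 1/0.522 = 1.92 times the patients of the baseline-adjusted analysis. With no effect, rejection rates were 4.2-5.6% for all methods.

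**4. Where the loss arises.** RE of B against C is (A/C)/(A/B). For the patient composite it is 0.540/0.863 = 0.63, rising to 0.797/0.929 = 0.86. The missing baseline thus costs 14-37% of the information, against 7-14% for the grouping, and is the larger share at every r. For the process composite it is 0.66, 0.75, 0.84 and 0.90. There the baseline share is larger at r = 0.30 and 0.50, and the grouping share is larger at 0.70 and 0.85.

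**5. Sensitivity.**
- A further run at 417 per arm with other assumed values gave, for A, B and C, 70-74%, 74-79% and 82-95% (patient) and 68-70%, 76-81% and 83-96% (process). The grouping then costs up to about 12 points and the total reaches about 26 (96 - 70).
- A clustered run (66 practices per arm, 9 analysed patients each, latent ICC 0.047) gave total losses of 4-15 points, the smallest where power was already above 90%.
- With fixed shifts not tuned to about 80% power, the grouping cost ranged from 1.1 (39.7 to 40.8%) to 6.8 (58.1 to 64.9%) on the patient score, and from 2.8 (93.9 to 96.7%) to 10.3 (64.5 to 74.8%) on the process score.

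**The case against.** The strongest reply is that this is a legitimate, if blunt, choice. Practices are randomised, so the baseline mix is balanced in expectation, and floor and ceiling act on both arms. The composites are secondary, with no power claimed. Two process items apply only to some patients, and how the others are scored is not stated. If the attainable maximum differs between patients, direction of change within a patient may compare better than a raw sum. The article cites a source for the composites, which may prescribe this scoring. Unconditional baseline adjustment is also absent for the continuous outcomes, so that part of the loss is not peculiar to the grouping. A ten-level ordinal model may be sparse, and its baseline-category fallback unwieldy.

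Most of this stands and limits the point to efficiency. It does not remove it: the article gives no reason for the grouping, and the conditional items need a scoring rule under either analysis. The group means mentioned under Primary and secondary outcomes are a summary, with no test of the full score attached.

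A reader might infer more, without support in the documents:
- That the comparison is biased or its error rate wrong. Randomisation and the null simulations speak against this.
- That the grouping discards most of the information. It removes most of the distinct values, but only 7-14% (patient) and 17-21% (process) of the information in the calibrated runs.
- That the whole power loss is due to the grouping. A large part is due to the missing baseline score.
- That offsetting changes are certainly unchanged. That needs a summation rule the text does not give.
- That baseline can never enter. Adjustment is allowed for imbalance, but this does not secure the precision gain.

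**Conclusion.** The point holds as a matter of efficiency, not validity. With effects giving the three-level test roughly 70-80% power, the grouping alone costs about 3-5 power points on the patient composite and 7-12 on the process composite. With the baseline score also left out, the total over all runs is roughly 4-26 points. At the upper end most of this comes from the missing baseline adjustment; on the process composite the two parts are closer, and their order depends on the baseline to follow-up correlation.

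The document gives none of the inputs that fix these sizes: item prevalences, item and baseline to follow-up correlations, effects, a 5% level for the composites, and the sign of the summed change as the grouping rule. The HbA1c sample size is also borrowed, and a single follow-up is used instead of four occasions. The direction was the same in all runs; the exact sizes are illustrative. The HbA1c primary outcome and its sample size are untouched.

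**What to change.** In Data analysis, make the tested outcome the follow-up composite score (0-3 for the patient composite; the process score as defined in Table 1), with the baseline composite score as a prespecified covariate whether or not the arms differ. Use the random-effects ordinal model already planned. If the ten-level process score is too sparse, use the linear mixed model already planned for continuous outcomes. State beforehand how the two conditional process items are scored for patients to whom they do not apply, in the same way at baseline and follow-up. Keep worsened/unchanged/improved as a descriptive or supportive table, and state how item changes combine into a category.

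The cost is a short change to the scoring and analysis text, with no new data or visits. The downsides are that the three-way category is no longer the tested outcome and that the conditional-item rule must be agreed first.
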